**Methods:**

Forty-six PSD patients will be randomized 1:1 to active or sham acupuncture (30 minutes sessions, 5 times per week for 6 weeks). The primary outcomes are rs-fMRI and DTI metrics reflecting functional and structural connectivity changes (ALFF, ReHo, FC, FA, MD). Secondary outcomes include Standardized Swallowing Assessment (SSA), videofluoroscopic swallowing study (VFSS)-based measures, Montreal Cognitive Assessment (MoCA), and Swallowing Quality-of-Life Questionnaire (SWAL-QOL). Twenty healthy volunteers will provide baseline neuroimaging reference data.

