**Figure 1 F1:**
[figure not shown]
Flow chart of the clinical trial procedures.

The trial has been prospectively registered in the Chinese Clinical Trial Registry (ChiCTR2400086748) on 10 July 2024. The trial registration was updated on 30 October 2025 to clarify the outcome hierarchy (rs-fMRI/DTI as the primary outcome; SSA/VFSS-based measures/MoCA/SWAL-QOL as secondary). No other changes were made.

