#### Primary outcome

2.7.2

Derived imaging metrics will be calculated from the acquired rs-fMRI and DTI data as described below. The primary neuroimaging outcomes are defined as the changes from baseline to week 6 in prespecified rs-fMRI metrics (ALFF, ReHo, and FC) and DTI metrics (FA and MD). In addition, 20 healthy controls will undergo baseline rs-fMRI and DTI examinations to provide a reference for PSD-specific neuroimaging alterations.

Rs-fMRI: Rs-fMRI is extensively utilized to probe the neural mechanisms of PSD. The rs-fMRI markers include amplitude of low-frequency fluctuations (ALFF), regional homogeneity (ReHo), and functional connectivity (FC), which can be used to reflect brain function in patients with PSD. However, existing research primarily emphasizes activation in localized brain regions, with insufficient exploration of acupuncture's effect on functional networks in PSD patients (17).

Therefore, we employed rs-fMRI to analyze brain functional network connectivity, aiming to further clarify the central mechanisms underlying acupuncture treatment for PSD.

ALFF: ALFF reflects the local activity level of specific brain regions by calculating signal strength in the 0.01–0.1 Hz frequency band. It is commonly utilized to explore activation patterns in various brain areas, facilitating our understanding of functional changes across different regions following a stroke, particularly those related to swallowing (18).ReHo: ReHo can capture local coherence changes within swallowing-network nodes (e.g., insula, M1, SMA) in PSD by measuring the temporal synchrony between a given brain region and its adjacent voxels, thereby assessing the consistency of neuronal activity within that region (19).FC: Functional connectivity assesses the interconnections between brain regions based on correlations in temporal sequences. Seed-based analysis (e.g., bilateral insula, M1 orofacial area, SMA) and independent component analysis (ICA) employ data-driven methods to capture broader network-level modulation. Evaluating overall connectivity patterns enhances our understanding of how acupuncture may improve neural network function in PSD patients (20, 21).

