### Sample size

2.9

This study is designed as an exploratory, mechanism-oriented neuroimaging trial. At present, there are limited prior data from sham-controlled acupuncture studies in post-stroke dysphagia that combine multimodal MRI outcomes with comparable clinical endpoints, which makes a formal power calculation based on a single anticipated effect size difficult. Therefore, the planned sample size was determined with reference to previous neuroimaging studies, practical feasibility, and the exploratory nature of the present protocol. Given the characteristics and high costs associated with neuroimaging studies, sample sizes are generally smaller compared with conventional clinical trials, and there is currently no standardized consensus regarding the minimum sample size required to achieve stable statistical power. A study in 2002 reported that a sample size of 12 subjects was sufficient to provide relatively stable statistical power in rs-fMRI research (39). In 2007, another study using auditory stimulation of rs-fMRI suggested that a sample size of 13–15 subjects was adequate for stable statistical inference (40). In 2011, investigators compared sample sizes of 5, 8, 14, 17, and 21 subjects under otherwise consistent conditions. They observed that smaller sample sizes (e.g., 5 or 8) produced fewer activation regions with greater variability, whereas larger sample sizes yielded more activation clusters and reduced intergroup differences (41). Ultimately, the literature recommends that, where ethically and practically feasible, neuroimaging trials should include at least 20 subjects per group (42).

Taking into account the constraints of study duration, patient hospitalization time, and available manpower, and with reference to previous clinical research, we determined that a randomized controlled trial with 20 participants per group (40 in total) would be appropriate. Considering an expected 15% dropout rate, the final planned sample size is 46 participants [40 × (1 + 15%) = 46].

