#### fMRI data analysis

2.11.1

Preprocessing and analyses will be conducted with SPM12, DPABI, and FSL. Functional and structural connectivity will be analyzed using independent component analysis (ICA) and canonical correlation analysis (CCA) (43–45). ROI-based analyses will prioritize prespecified swallowing-related hubs (the insula, basal ganglia, frontal cortex, M1, SMA, corona radiata, and S1) as the primary ROI set for functional and structural connectivity tests. Network-level extensions (e.g., the default mode network (DMN), the frontal-temporal-sensory-motor circuit, the sensory-motor-insular-thalamic circuit and the insula-cerebellum-occipital circuit) will be reported as secondary/supportive analyses with appropriate multiple-comparison control. Structure–function coupling will be assessed by examining the relationship between functional connectivity and structural connectivity between corresponding brain regions. Functional connectivity (FC) will be calculated as the Pearson correlation between the BOLD time series of predefined regions of interest (ROIs). Structural connectivity will be derived from diffusion tensor imaging using probabilistic tractography to identify white-matter fiber tracts connecting the same ROI pairs. For each tract, the mean fractional anisotropy (FA) along the reconstructed fibers will be calculated to represent the integrity of the structural pathway. Structure–function coupling will then be evaluated by assessing the relationship between FC strength and tract-specific FA values across ROI pairs (46). In addition to the hypothesis-driven ROI analyses, exploratory whole-brain analyses will be conducted to identify potential PSD-related brain regions beyond the predefined swallowing network. Voxel-wise comparisons of rs-fMRI metrics (e.g., ALFF and ReHo) will be performed across the whole brain between groups. Statistical analyses will be conducted using a general linear model framework, and multiple comparisons will be controlled using false discovery rate (FDR) correction (p < 0.05). This will allow us to assess how acupuncture modulates the interaction between structural integrity and functional network organization in PSD.

To correct for multiple comparisons, we will apply the false discovery rate (FDR) at the voxel level and Bonferroni correction for network-level metric (47).

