Post-stroke dysphagia (PSD) occurs when cerebral infarction disrupts the distributed neural system that supports swallowing, leading to abnormalities in both network connectivity and white-matter integrity. Importantly, converging neuroimaging evidence suggests that PSD is best conceptualized as a network-level disorder rather than a focal lesion effect, involving coordinated dysfunction across cortical and subcortical hubs. At the cortical level, swallowing-related control engages the sensorimotor cortex (M1/S1/S2), SMA, and frontal regions (including IFG), and interacts closely with subcortical structures such as the thalamus, insula, and basal ganglia, as well as bottleneck white-matter regions (e.g., corona radiata/internal capsule) (55). Recent work has further described modular organization within the swallowing connectome (e.g., insula, cerebellum, sensorimotor–cingulate, IFG–S2–corpus callosum–basal ganglia–thalamus, and premotor–posterior parietal modules), which can be arranged into higher-order circuits supporting swallowing control and compensation (55). Notably, prior rs-fMRI studies in PSD have reported both regional activity alterations and connectivity abnormalities across these hubs, including the sensorimotor cortex, insula, cerebellum, cingulate, thalamus, and basal ganglia (56). Across studies, the most frequently implicated loci include the insula, basal ganglia, frontal cortex, M1, SMA, corona radiata, and S1(57). However, brain network–level evidence remains limited, and existing studies have only partially examined how these regions reorganize as integrated circuits during recovery. For example, rs-fMRI and fNIRS studies suggest abnormalities in DMN and reduced connectivity between the frontal–temporal–sensory–motor circuit and the sensory–motor–insular–thalamic circuit; moreover, altered insula–cerebellum–occipital functional connectivity has been associated with dysphagia severity (51, 58).

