Therefore, in the present study we explicitly separate primary and secondary analyses. The primary (confirmatory) analyses anchor structure-function coupling tests to a prespecified ROI set that captures core swallowing-related hubs with consistent PSD abnormalities (insula, basal ganglia, frontal cortex, M1, SMA, corona radiata, and S1). The secondary (supportive) analyses extend to larger-scale circuits (DMN, frontal–temporal–sensory–motor, sensory–motor–insular–thalamic, and insula–cerebellum–occipital circuits) and are interpreted as hypothesis-generating.

DTI provides complementary insight into the microstructural substrates of PSD. The severity of white-matter injury—reflected by FA and MD metrics—is closely related to the severity of dysphagia, and adaptive white-matter changes may accompany recovery (59). Stroke is associated with disturbances of both functional and structural networks and with state-dependent reductions in functional-structural coupling (60). Therefore, this study included 20 healthy controls as a baseline reference to identify network sites with PSD abnormalities. Combined rs-fMRI and DTI analyses of SC-FC coupling sensitively index clinical impairment and recovery after PSD (46, 60).

Rs-fMRI studies indicate that acupuncture can activate swallowing-related cortical regions in PSD and enhance activity within central swallowing hubs, thereby promoting functional recovery of the cortical swallowing centers. FNIRS evidence suggests that acupuncture facilitates frontotemporal-sensorimotor network integration (61). However, PSD involves not only widespread cortico-cortical injury but also disruption of cortico-subcortical networks, and the mechanisms of structure-function reorganization remain insufficiently understood (51).

Building on this analysis hierarchy, we will examine whether acupuncture-related changes in structure-function coupling and circuit-level functional connectivity track clinical improvement over the 6-week intervention period, using healthy controls as a baseline reference.

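### Structure-function coupling is called the primary, confirmatory analysis in the Discussion, but it is not among the five defined primary outcomes and the trial is described as exploratory

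*Protocol article*

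**What the plan says.** Five places in the protocol article bear on which imaging analysis is primary.

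- **Section 2.7.2, Primary outcome:** "The primary neuroimaging outcomes are defined as the changes from baseline to week 6 in prespecified rs-fMRI metrics (ALFF, ReHo, and FC) and DTI" metrics, the latter being FA and MD. The Abstract (Methods) names the same five.
- **Section 2.1, Registration and trial design:** the registered hierarchy puts rs-fMRI/DTI first and the clinical scales second. It names no single metric and does not mention coupling.
- **Section 2.11.1, fMRI data analysis:** seven hubs (insula, basal ganglia, frontal cortex, M1, SMA, corona radiata, S1) serve "as the primary ROI set for functional and structural connectivity tests". Coupling is described afterwards and is not labelled primary.
- **Section 3, Discussion:** "The primary (confirmatory) analyses anchor structure-function coupling tests to a prespecified ROI set that captures core swallowing-related hubs with consistent PSD abnormalities". Larger circuits are secondary and hypothesis-generating.
- **Section 2.9, Sample size:** "This study is designed as an exploratory, mechanism-oriented neuroimaging trial". The section explains why there is no formal power calculation.

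On the corona radiata, section 2.11.1 takes FC as the Pearson correlation of BOLD series between the regions and looks for tracts joining the same pairs. The Discussion places this structure among "bottleneck white-matter regions (e.g., corona radiata/internal capsule".

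**The concern.** A reader who asks which imaging analysis is primary gets two answers: five metrics that exclude coupling, or coupling tests. A reader who asks whether that analysis is meant to confirm or to explore also gets two answers.

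This affects what may be concluded. A positive coupling test could be presented as confirmatory on the strength of the Discussion, although neither the outcome definition nor the registered hierarchy lists it and no sample size was derived for it. The label also has an operational use: section 2.4 allows unblinding only after database lock and the primary analyses, so that trigger depends on which analyses count as primary.

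The corona radiata adds a problem inside the coupling measure. A coupling pair needs two end regions and a tract between them. A white-matter region is part of the pathway, so using it as an end region mixes the two sides of the comparison.

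**Working it through.** **1. The plan's own figure.** Section 2.9 gives 40 × (1 + 0.15) = 46, which reproduces. It rests on a convention of 20 per group and is tied to no outcome, so it does not show which analysis is meant to be decisive.

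**2. The statements side by side.**

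| Place | Primary | Coupling included? | Status |
|---|---|---|---|
| Abstract; 2.7.2 | ALFF, ReHo, FC, FA, MD | No | Not labelled |
| 2.1 (registered hierarchy) | rs-fMRI/DTI | No | Not labelled |
| 2.11.1 | FC and structural connectivity tests in seven hubs | Described, not labelled primary | Not labelled |
| Discussion | Coupling tests in the same hubs | Yes | Confirmatory |
| 2.9 | – | – | Exploratory (whole trial) |

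**3. Is coupling covered by listing FC and FA?** No. The primary outcomes are changes over time in each metric. Coupling is the relation between FC strength and tract FA across region pairs. FC and FA could both rise with no change in how they relate across pairs, and the relation could change while the average FC and FA stay the same. The multimodal text under section 2.7.2 says only that the approach may shed light on coupling; it does not define coupling as an outcome.

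**4. Reach of the corona radiata.** The documents do not say how many regions each hub contributes, so this count needs an assumption.

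- One region per hub: 7 × 6 / 2 = 21 pairs. Pairs containing the corona radiata: 6. Share: 6/21 = 29%. Pairs left without it: 15.
- Every hub split into left and right: 14 × 13 / 2 = 91 pairs. Pairs without either corona radiata: 12 × 11 / 2 = 66. Pairs with at least one: 91 − 66 = 25. Share: 25/91 = 27%.

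Under either assumption, more than a quarter of the pairs are affected.

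**The case against.** The strongest defence is that the Discussion paragraph mainly separates the core hubs from the larger circuits, as section 2.11.1 does. On that reading it says where coupling tests are anchored and does not replace the outcome list. The word confirmatory is also never applied to the five metrics, and a mechanism study that declares itself exploratory need not have one deciding endpoint. This softens the conflict but does not remove it: the sentence still gives coupling the primary and confirmatory label, which the outcome section withholds. An unseen analysis plan could add a decision rule, but the article's statements would still disagree.

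For the corona radiata, the authors may intend it only for the structural tests. That is plausible, but one list serves both kinds of test and no exception is stated.

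Three stronger readings are tempting and are not supported.

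- **A late switch of the primary outcome.** A reader might note that "The trial registration was updated on 30 October 2025 to clarify the outcome hierarchy", day 464 of a planned 526-day recruitment window that opened on 23 July 2024 (464/526 = 88%). As section 2.1 describes it, that update ranks imaging above the clinical scales and says nothing of coupling. The previous registry text is not shown. Section 2.15 already gives the recruitment dates and says the data remain blinded with no primary outcome analyses done.
- **A power failure.** Detectable differences could be computed for about 20 per arm, but the trial claims no power and lists its small sample as a limitation. Such figures do not measure a conflict of labels.
- **Coupling as the sole primary.** This would change the primary outcome at a still later date, since the article appeared in June 2026, after the planned end of recruitment. It would also demote all five metrics that the trial did define.

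**Conclusion.** The contradiction stands and can be checked by reading. The defined primary outcome is five metrics without coupling; the Discussion makes coupling the primary, confirmatory analysis; section 2.9 makes the whole trial exploratory. No arithmetic is needed for this, and no misconduct or outcome switching is implied. The consequence is limited but real: a confirmatory claim could be attached to an analysis that was neither defined as primary nor given a sample-size basis.

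The corona radiata fault is smaller and separate. It affects 29% of pairs with one region per hub and 27% with left and right split; both counts assume that all pairs among the listed hubs are used.

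**What to change.** 1. Keep ALFF, ReHo, FC, FA and MD, as change between baseline and week 6, as the primary outcomes. The Abstract, section 2.7.2 and the registered ranking then need no change.
2. In section 2.11.1 and the Discussion, label structure-function coupling a prespecified secondary analysis.
3. Delete the word confirmatory from the Discussion and report all imaging results as exploratory, in line with section 2.9. The distinction between core hubs and larger circuits can stay.
4. In section 2.11.1, state that the corona radiata is used for FA and MD only and is left out of the FC and coupling pairs.

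The cost is wording in the protocol and any analysis plan, with a correction to the article; no new data are needed. The change should be made and dated before unblinding. The downside is that no confirmatory claim can be made for coupling, and the coupling measure rests on fewer pairs (15 instead of 21 with one region per hub).

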## Conclusions

4

In conclusion, this randomized controlled trial employing rs-fMRI and DTI is designed to assess both the clinical efficacy and the central neural mechanisms of Tiao Shen Li Yan acupuncture in PSD. The results are expected to provide objective evidence regarding the clinical efficacy and neural mechanisms of acupuncture and to serve as a valuable reference for evidence-based PSD management guidelines.
